## non-inclusion criteria

Patients presenting the following characteristics will not be included:

- History of myeloproliferative syndrome, transient myeloproliferative disorder, leukaemoid reaction or neonatal thrombocytopenia,

- Current infantile seizures, unbalanced epilepsy,

- The initiation of thyroid hormone treatment in the three months preceding the trial (patients on stable treatment with thyroid extracts[[13]](#footnote-2) for more than three months may be included),

- Patients presenting folinic acid intolerance.

## exclusion criteria

Patients will be removed from the study if one of the following criteria is met:

- Occurrence of myeloproliferative syndrome;
- Initiation of thyroid hormone treatment during the study (patients already on stable thyroid extract treatment for more than 3 months may be included);
- Folic or folinic acid treatment (other than that studied) for more than two months during the trial: Alvityl®, Azedavit®, Azinc®, Carencyl®, Cernevit®, Elevit®, Elvorine®, Folinate de calcium, Folinoral®, Forvital®, Léderfoline®, Lofenalac®, Osfolate®, Perfolate®, Plenyl®, Quotivit®, Soluvit®, Spéciafoldine®, Synergyl®, Tardyféron®, Vivamyne®, Zédène®,
- Treatment with a drug with antifolate activity for more than two months of the year (methotrexate, phenytoin).

For patients withdrawing early from the trial, as much information as possible will be obtained by telephone and the final examination will be carried out as soon as possible (within a month of withdrawal).

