## trial description and chronology

The total duration of follow-up for any given patient in the trial will be 1 year ± 30 days.

The first medical consultation will include:

- Information about the trial and the signing of the consent form;
- Confirmation of the diagnosis, checking for the presence of karyotyping data in the patient's medical records;
- Checking the inclusion and non-inclusion criteria, including, in particular, ability to undergo the revised Brunet-Lezine test for determining developmental age (DA);
- A general clinical and neurological examination, with measurement of height, weight and CC;
- Prescription of routine biological tests (blood formula, iron, ferritin, thyroid assessment) and other specific examinations, if necessary.

The first consultation with the psychologist will include a psychological examination and the revised Brunet-Lezine test.

Intermediate contact will be made with the parents at intervals of no more than two months. During these intermediate contacts by telephone, the interview by a doctor from the CMJL will focus particularly on the tolerance of folinic acid treatment.

If necessary, the final consultation may take place early, in cases of withdrawal from the study.

The intermediate consultation (6 months ± 15 days) and the final visit (1 year ± 30 days) will include:

- A general clinical and neurological examination, with measurement of height, weight and CC;

- The recording of any adverse events;

- The recording of the doctor's opinion concerning the child (CGI);

- The recording of the overall opinion of the psychologist concerning the development and behaviour of the child on a visual analogue scale (VAS);

- The revised Brunet-Lezine test (determination of DA);

- The recording of the parents' opinion on the treatment of the child;

- The prescription of routine biological tests (blood formula, iron, ferritin, thyroid assessment) and other specific examinations if required.

The entire study will therefore include only standard examinations: three medical examinations, three psychological examinations and three sets of standard biological tests. Between consultations, three to five telephone contacts are planned to help the family and for the monitoring of tolerance and compliance with treatment. If possible, all the examinations will take place on the same day, with the same doctor and the same psychologist.

The total duration of the inclusion period will be 1.5 years.

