### Emergency decoding

A set of envelopes making individual decoding possible will be stored at the Centre Médical Jérôme Lejeune. Treatment decoding will be allowed only if knowledge of the treatment administered is liable to modify subsequent treatment. In this trial, there should therefore be no need to open the emergency decoding envelopes.

However, in cases of emergency decoding, the name and signature of the person responsible for the decoding will be noted on the decoding envelope and in the observation notebook, together with the date, time and reason for decoding and action taken as a result. The opened decoding envelope will be placed in the pocket of the observation notebook. The time of decoding will mark the end of the observation period for the subject concerned.

In no case will these envelopes be used for decoding at the end of the trial.

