### Efficacy

Efficacy will be evaluated using several criteria.

The principal evaluation criterion will be the change in developmental age, the profile of which is known for patients with Down's syndrome [[[16]](#endnote-16)]:

Translation for the figure: Age mental = mental age; Age reel = real age.

Developmental age will be assessed by the revised Brunet-Lezine test administered before (DA0) and after (DAf) treatment: (DAf - DA0). The revised Brunet-Lezine test is widely recognised as a test for the evaluation of psychomotor development in infants. It has been validated and its metrological qualities (sensitivity, fidelity-homogeneity, dispersion and validity, including for Down's syndrome children) are well known. For further information about this test, please consult reference 13.

The other criteria for efficacy evaluation will be:

- CGI, as recorded by the doctor;
- A score for psychologist satisfaction, estimated on a VAS, evaluating the opinion of the psychologist on the subjective improvement of the child since the start of treatment.
- The response of the parents to the question "If possible, would you like to continue this treatment ?" The response will be scored as follows: in favour of continuing treatment/against continuing treatment/does not know or no opinion expressed.

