# losses to follow-up and premature withdrawal from the trial

The reasons for which a subject may be withdrawn from the trial are as follows:

- Demand from the patient, withdrawal of consent;
- Clear aggravation;
- Occurrence of a serious or unpleasant adverse effect associated with the product tested;
- Poor compliance
- Occurrence of myeloproliferative syndrome;
- Initiation of thyroid hormone treatment during the trial (patients already on thyroid extracts treatment for more than 3 months may be included);
- Treatment with folic or folinic acid (other than the product studied) for more than two months during the trial.

The reasons for the treatment being stopped early or for premature withdrawal from the trial should be documented and reported clearly in the observation notebook, on the appropriate page. All cases of premature cessation of treatment or withdrawal will be analysed in terms of tolerance and efficacy, provided that it is possible to obtain the appropriate data.

The number of subjects lost to follow-up should be minimised and as much information as possible should be collected for these subjects (by postal or telephone contact, for example).

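### Children who leave early contribute a gain over less than one year to the unscaled primary criterion, and two rules for their final value are unreconciled

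*Protocol*

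**What the plan says.** **Length of follow-up.** Protocol, *trial description and chronology*: "The total duration of follow-up for any given patient in the trial will be 1 year ± 30 days". The same section adds: "If necessary, the final consultation may take place early, in cases of withdrawal from the study". That consultation includes the Brunet-Lezine test.

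**Early withdrawal.** *Exclusion criteria* lists events after entry that lead to mandatory removal, for example "Initiation of thyroid hormone treatment during the study". The others are myeloproliferative syndrome and more than two months of other folates or of antifolate drugs. For early withdrawals, "the final examination will be carried out as soon as possible (within a month of withdrawal".

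**Further reasons.** *Losses to follow-up and premature withdrawal from the trial* lists reasons for which a child may be withdrawn. They include clear aggravation, poor compliance and an adverse effect associated with the product. It adds: "All cases of premature cessation of treatment or withdrawal will be analysed in terms of tolerance and efficacy", if the data can be obtained.

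**Decoding.** *Emergency decoding*: "The time of decoding will mark the end of the observation period for the subject concerned".

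**Missing final test.** *Missing data* treats the intermediate examination as the final one for a child who does not return at one year. A child with no data after the initial examination counts as missing.

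**Primary criterion and test.** *Efficacy*: "Developmental age will be assessed by the revised Brunet-Lezine test administered before (DA0) and after (DAf) treatment: (DAf - DA0". The abbreviation list assigns f to the final examination. *Tests used* compares the change If - I0 by t test, or by Mann-Whitney if the data cannot be normalised.

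**Sizing.** *Number of cases* assumes one-year gains of 0.666 years (placebo) and 0.900 years (folinic acid), SD 0.4 and 80% power. It arrives at 47 per group and plans 50 per group, counted as 100 complete observations.

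**The concern.** Developmental age rises with time in children of this age, treated or not. A gain measured over four or six months is therefore smaller than a one-year gain for reasons unrelated to folinic acid. The criterion is an unscaled difference, and nothing in the protocol adjusts it for the interval between tests.

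Mixing intervals does two things. It widens the spread and shrinks the contrast, which costs power. If the arms differ in how many children leave, or when, it also creates a difference between arms with no treatment effect behind it.

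The protocol settles when children are tested and when observation stops, so an analysis plan cannot repair this later: a 12-month test that was never taken cannot be recovered.

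**Working it through.** **1. Which value enters for a child who leaves?**

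- *Leaves after month 6 and is tested on leaving.* The *exclusion criteria* rule gives a test at, say, month 8. The *missing data* rule gives the month-6 test, because this child also does not return at one year. Both rules apply and no order is stated.
- *Leaves before month 6 and is tested on leaving.* Only the early test exists.
- In each case the available value covers less than a year.

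**2. The plan's own figure.** Inputs from *number of cases*: difference 0.900 - 0.666 = 0.234 years, SD 0.4, two-sided alpha 0.05, power 80%. The exact two-sample t test needs 46.85 per group, so 47, as stated. Power is 80.1% at 47 per group and 82.5% at 50.

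**3. Expected gain at an early test** (assumption: gain is linear in time)

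| Last test | Placebo | Folinic acid |
|---|---|---|
| Month 3 | 0.666 × 3/12 = 0.167 | 0.900 × 3/12 = 0.225 |
| Month 6 | 0.666 × 6/12 = 0.333 | 0.900 × 6/12 = 0.450 |
| Month 12 | 0.666 | 0.900 |

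**4. Effect on the comparison.** Let a share w of an arm with one-year gain g be last tested at month m, and let f = m/12.

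- Arm mean: g × (1 - w(1 - f))
- Arm variance: 0.4² + w(1 - w) × (g(1 - f))²
- Standard error of the difference: √((sum of the two variances)/50). Power comes from the noncentral t distribution with 98 degrees of freedom.

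Worked case, w = 10% in both arms, month 6:

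- Means: 0.900 × 0.95 = 0.855 and 0.666 × 0.95 = 0.633; difference 0.222.
- Variances: 0.16 + 0.09 × 0.450² = 0.178 and 0.16 + 0.09 × 0.333² = 0.170.
- Standard error: √(0.348/50) = 0.083. Power: 75%.

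Equal shares leaving, planned effect true:

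| Share in each arm | Month 6: difference, power | Month 3: difference, power |
|---|---|---|
| 0% | 0.234, 82.5% | 0.234, 82.5% |
| 10% | 0.222, 75% | 0.216, 69% |
| 20% | 0.211, 68% | 0.199, 56% |

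With equal shares and no true effect, type I error stays at 5%.

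Unequal shares, 20% on folinic acid and 10% on placebo:

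| | Month 6 | Month 3 |
|---|---|---|
| No true effect: difference | 0.666 × (0.90 - 0.95) = -0.033 | 0.666 × (0.850 - 0.925) = -0.050 |
| No true effect: type I error | 6.8% | 8.7% |
| Planned effect: difference | 0.900 × 0.90 - 0.666 × 0.95 = 0.177 | 0.900 × 0.850 - 0.666 × 0.925 = 0.149 |
| Planned effect: power | 54% | 37% |

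With the shares exchanged between arms, the false difference is +0.033 or +0.050.

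**5. What 12-month testing would recover.** Further assumption: a child who stops folinic acid keeps the gain so far and then grows at the placebo rate. The difference is then 0.234 × (1 - w(1 - f)), with w the share stopping on folinic acid. The variance is 0.16 on placebo and 0.16 + w(1 - w) × (0.234(1 - f))² on folinic acid.

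- 10% stopping: difference 0.222 and power 78% (month 6); 0.216 and 76% (month 3).
- 20% stopping: difference 0.211 and power 74% (month 6); 0.199 and 69% (month 3).
- With no true effect the difference is zero, whatever the shares.

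The remaining loss is dilution from stopping treatment. Testing everyone at 12 months removes the part caused by unequal intervals.

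**The case against.** **The early test is not expressly made the primary value.** Testing a child on leaving is sound data collection, and the protocol never says outright that this test enters the primary t test. This stands, and it is why the point is put as two unreconciled rules. It does not remove the problem: by the protocol's notation the final examination supplies DAf, withdrawals go into the efficacy analysis, and the alternative rule also shortens the interval.

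**Removal is narrower than it may look.** A reader might infer that every listed reason forces a child out of the study. Only the *exclusion criteria* events are mandatory; the longer list gives reasons for which withdrawal may happen. The sections on dose and on adverse effects let treatment stop without saying that the child leaves. *Emergency decoding* expects no decoding and mentions no early test.

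**Treatment-related truncation is not shown.** A reader might conclude that selective withdrawal breaks the randomised comparison. The documents do not support this. A product-associated adverse effect or clear aggravation can depend on treatment or development. For the mandatory triggers a link to arm is possible but not stated. The protocol selects for likely compliance and describes tolerance as excellent, so it gives no ground to expect unequal withdrawal. If withdrawal is balanced, the harm is lost power.

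**The size is assumed.** The protocol gives no withdrawal rate, and linear growth is a simplification. At low, slightly unequal rates (10% on folinic acid, 5% on placebo, tested at month 4) the false difference is only -0.022 years and type I error about 5.8%, while power is about 63%. One child's shortfall should not be set against the group difference of 0.234 as if it measured bias in the trial.

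**Conclusion.** The point holds as a weakness in follow-up after withdrawal. Two rules compete for the final value of a child without a one-year test, and both put a shorter-interval gain into a criterion sized on one-year gains.

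If 10% to 20% of each arm leave, the likely cost is power: 82.5% falls to between 75% and 56%, depending on the share and on the month of the last test. A false difference between arms needs unequal withdrawal. At 20% against 10% it is 0.033 to 0.050 years, against the arm with more departures, with type I error of 6.8% to 8.7%. These figures rest on assumed withdrawal shares, linear growth, SD 0.4 and 50 per arm.

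A reader might also infer that a 12-month result is thrown away. It is not: under these rules the test is never taken. Severity: SHOULD-FIX.

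**What to change.** Separate the end of treatment from the end of follow-up. No rule on dose or on stopping treatment changes.

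- **Follow-up** (*trial description and chronology*, *exclusion criteria*, *losses to follow-up*, *Emergency decoding*): every randomised child whose parents have not withdrawn consent keeps the scheduled 6- and 12-month Brunet-Lezine tests, whatever happens to treatment and also after decoding.
- **Final value** (*missing data*, together with the two early-examination rules): neither an early test nor the 6-month test is used as DAf.
- **Analysis population** (*data input, decoding and analysis*): analyse all randomised children in their allocated group.
- **Method** (*Tests used*): model developmental age over time since entry, with each test at its actual date, and estimate the 12-month difference. An early test from a child whose parents refuse the 12-month visit then contributes without standing in for it.

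Cost: wording in seven sections, a modest change of analysis method, and attendance at visits already in the schedule. The estimate will include children who stopped treatment or took other folates, so the contrast is diluted (step 5 of the working gives the size). Parents who withdraw consent cannot be held to further tests, so some missing data will remain.

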# treatments

## product studied: folinic acid

Folinic acid will be administered in the form of Folinoral® (calcium folinate), formulated appropriately for this trial. The characteristics of Folinoral® can be found in the monograph from the Vidal guide provided in the appendix.

### Presentation, formulation and labelling

The labelling and presentation of the product will conform to the legislation in force (Article R5123 of the French Public Health Code).

The product will be presented in the form of capsules to be taken *per os*. These capsules will in no case be administered in this form. They will always be opened and their content mixed with some cold food (yoghurt, compote, jam) to prevent any possible degradation, although the product is stable. Folinic acid is almost tasteless.

The capsules of the active product will contain 5 mg of folinic acid in the form of the pentahydrated carbon salt of N‑[[[(amino‑2 formyl‑5 hydroxy‑4 tetrahydro‑5,6,7,8 pteridinyl‑6) methyl] amino]‑4 benzyl] glutamic acid and excipients.

The placebo will be presented in a strictly identical manner and will be composed of inactive excipients.

The parents will be provided with the treatment on the day of the first consultation and on the day of the intermediate consultation. On both occasions, they will be provided with enough capsules for 6.5 months (196 days) of treatment (about 50% of the patients are from outside the Parisian region). All of the blister packs of treatment, whether empty or full, must be brought to each consultation.

### Dose and duration of treatment

The dose used will be 1.0±0.3 mg/kg/d at the start of treatment. This dose is relatively high, to ensure that no effect is missed. Folinic acid is non-toxic. No overdose has been observed, even during the administration of very high doses. Indeed, once the amount required has been used, the excess is eliminated (see the section from the Vidal provided in the appendix).

The table below shows the dose to be administered as a function of weight.

WEIGHT (kg) DOSE (mg) No. CAPSULE

These doses are high because the dose in mg/kg is likely to decrease as the child grows during the observation period. At the ages studied, the children are unlikely to put on more than 3 kg per year, so the dose should never fall below 0.7 mg/kg. The dose could be increased as a function of weight, without exceeding 20 mg/d, at the time of the intermediate consultation or telephone contact. Any such change in dose will be recorded in the "treatment and rehabilitation" section of the observation notebook.

In cases of functional problems, such as irritability or hyperactivity, the dose may be progressively decreased, by one capsule per day, by the investigator. If the symptoms persist or are too severe, the investigator could stop the treatment early. If possible, the patient should be re-evaluated at a consultation before the treatment is stopped.

The total duration of treatment will be 1 year ± 1 month. The product will be administered as a single intake at breakfast.

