## inclusion criteria

Patients with the following characteristics will be included:

- Down's syndrome (free and homogeneous trisomy 21),

- Suitability for assessment with the revised Brunet-Lezine test at the time of the first examination and (predictively) the second examination. Children should thus be aged between about six and 24 months,

- Weight between 6 and 26 kg,

- Planned stable maintenance treatment for the next year,

- Good compliance likely and possibility of carrying out subsequent examinations within the required time frame,

- Patient resident in France

- Parent or guardian of the child contactable by telephone,

- Parent or guardian having received and understood the information document and signed the informed consent form.

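### With whole 5 mg capsules, the starting range and the 0.7 mg/kg floor cannot both hold for children entering at about 6 to 7.69 kg

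*Protocol*

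**What the plan says.** Four places in the protocol bear on this.

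- *Dose and duration of treatment* sets the start: "The dose used will be 1.0±0.3 mg/kg/d at the start of treatment". A table then converts weight to dose and capsules; only its header, "WEIGHT (kg) DOSE (mg) No. CAPSULE", is in the text available. The section explains that mg/kg will decline with growth and concludes that "the children are unlikely to put on more than 3 kg per year, so the dose should never fall below 0.7 mg/kg". It continues: "The dose could be increased as a function of weight, without exceeding 20 mg/d, at the time of the intermediate consultation or telephone contact". For functional problems, "the dose may be progressively decreased, by one capsule per day, by the investigator".
- *Presentation, formulation and labelling*: "The capsules of the active product will contain 5 mg of folinic acid". Capsules are opened and stirred into cold food. Giving part of a capsule is neither provided for nor ruled out.
- *Inclusion criteria*: "Weight between 6 and 26 kg", with age about six to 24 months.
- The schedule table under *design of the trial* plans weighing at months 0, 6 and 12, and none at the telephone contacts.

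**The concern.** The floor of 0.7 mg/kg is presented as following from the starting dose and a limited weight gain. But 0.7 is also the bottom of the starting range, so a child who starts near it falls below it with almost any growth. Whether the floor holds therefore depends on the dose steps available at each weight. A 5 mg step is coarse for a child of 6 or 7 kg, where one capsule more or less changes the dose by 0.7 to 0.8 mg/kg.

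What is at stake is how the result is read. The protocol calls its dose relatively high so that no effect is missed. If part of the active arm could drift well under the stated floor, a negative result would be harder to interpret, and a reader relying on that sentence would not know it. The endpoint, the sample size and the planned tests are not touched.

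**Working it through.** **Inputs.** Starting range 0.7 to 1.3 mg/kg, gain up to 3 kg, floor 0.7 mg/kg and limit 20 mg/d (*Dose and duration of treatment*); 5 mg step (*Presentation, formulation and labelling*); entry weight 6 to 26 kg (*inclusion criteria*). Assumption: whole capsules, so D is 5, 10, 15 or 20 mg.

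**Conditions for entry weight w.** Start: 0.7 ≤ D/w ≤ 1.3, so D/1.3 ≤ w ≤ D/0.7. Floor with the dose unchanged: D/(w+3) ≥ 0.7, so w ≤ D/0.7 − 3.

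| D (mg) | Start range met for w (kg) | Floor kept after +3 kg for w up to (kg) |
|---|---|---|
| 5 | 3.85 to 7.14 | 4.14 |
| 10 | 7.69 to 14.29 | 11.29 |
| 15 | 11.54 to 21.43 | 18.43 |
| 20 | 15.38 to 28.57 | 25.57 |

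**Where the protocol's floor is reproduced.** From 7.69 to 11.29 kg (10 mg) and from 11.54 to 25.57 kg (15 or 20 mg), some whole-capsule dose meets both conditions. For example, 10 mg at 8 kg starts at 10/8 = 1.25 and ends at 10/11 = 0.91 mg/kg. The statement is attainable over most of the admitted range.

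**Where it is not: low weights.**

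| Entry weight (kg) | One capsule: start, then after +3 kg (mg/kg) | Two capsules: start, then after +3 kg (mg/kg) |
|---|---|---|
| 6 | 0.83, 0.56 | 1.67, 1.11 |
| 7 | 0.71, 0.50 | 1.43, 1.00 |
| 7.14 | 0.70, 0.49 | 1.40, 0.99 |
| 7.4 | 0.68, 0.48 | 1.35, 0.96 |
| 7.69 | 0.65, 0.47 | 1.30, 0.94 |

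- *6 to 7.14 kg.* Only one capsule meets the starting range. It would keep the floor after +3 kg only for entry weights up to 4.14 kg, below the admission limit. Two capsules keep the floor but start above 1.3 mg/kg.
- *7.14 to 7.69 kg.* One capsule is under 0.7 and two are over 1.3. The worst case is where the two misses are equal: 0.7 − 5/w = 10/w − 1.3, so w = 15/2.0 = 7.5 kg. The choices there are 0.667 and 1.333, a miss of 0.033 mg/kg.

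**Other gaps at +3 kg.** From 11.29 to 11.54 kg the miss is slight: at 11.4 kg, 10 mg ends at 10/14.4 = 0.694 and 15 mg starts at 15/11.4 = 1.316. From 25.57 to 26 kg the limit binds: 20/26 = 0.77 at start and 20/29 = 0.69 after 3 kg, with no increase allowed.

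**Sensitivity to the gain.** With a gain of 2 kg the low-weight gap is still 6 to 7.69 kg. With 1 kg it is about 6.15 to 7.69 kg, since 7.14 − 1 = 6.14.

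**Timing.** If the gain is 3 kg and linear over the year (an assumption), a 6 kg child on one capsule passes 7.14 kg after 1.14/3 × 12 = 4.6 months, and a 7 kg child after 0.14/3 × 12 = 0.6 months. Both fall before the scheduled six-month weighing.

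**Sensitivity to capsule splitting.** With 2.5 mg steps, 7.5 mg gives 1.25 then 0.83 at 6 kg, and 0.975 then 0.702 at 7.69 kg. The low-weight gap and the one near 11.4 kg close; only 25.57 to 26 kg remains.

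**The case against.** The strongest reply is that the operative rule is the dose table, and its rows are not in the available text. That stands in part. The rows would show which condition fails: two capsules at 6 kg would keep the floor and break the starting range. They could not remove the conflict, because with whole capsules any row for about 6 to 7.69 kg breaks one or the other. A reader might infer that the lightest children end the year on about half the nominal dose. That needs the one-capsule row, the full 3 kg and no adjustment, so the documents do not establish it.

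Second, whole capsules are inferred. The capsule-number column, reductions by one capsule and compliance by capsule count all point that way, but capsules are opened before use and nothing forbids splitting. This stands as a condition on the finding.

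Third, the dose may be raised with weight, and contacts are at most two months apart. A timely increase could hold the floor at 6 to 7.14 kg and would not breach the ±0.3, which is stated only for the start. But the floor is inferred from growth alone before any increase is mentioned, the increase is optional, and no weighing is scheduled between month 0 and month 6. Nor can an increase mend the start at 7.14 to 7.69 kg.

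Fourth, the wording is soft. It is a statement of expectation, and it would be too much to say the protocol declares a lower dose impossible. Still, granting the stated gain, the conclusion does not follow at these weights.

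Two further inferences should be resisted. The background argues for treating young children in general; it does not say that the lightest of those enrolled would respond most. And a one-capsule reduction that takes a one-capsule child to zero is not a contradiction: the same section allows early stopping, and the floor concerns growth.

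**Conclusion.** The point holds, on the condition that doses are whole 5 mg capsules. For entry weights of about 6 to 7.69 kg, the starting range, the 6 kg lower limit and the 0.7 mg/kg floor after a gain of up to 3 kg cannot all be true. The material part is 6 to 7.14 kg, where the only dose within the starting range would, if unchanged, end at 0.56 to 0.49 mg/kg after 3 kg. The starting gap at 7.14 to 7.69 kg is small, at most about 0.03 mg/kg for the nearer dose, and the shortfalls near 11.4 kg and at 25.6 to 26 kg are marginal.

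Which condition fails in practice is not known without the table rows. The protocol gives no distribution of entry weights, so the share of children affected cannot be stated; only those on active drug would have lower exposure. This is an incorrect dose statement that should be put right. It is not a flaw in the trial's design or analysis.

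**What to change.** Reconcile *inclusion criteria*, *Presentation, formulation and labelling* and *Dose and duration of treatment*, so that the weight range, capsule strength, starting range, expected gain, floor and upper limit agree with one another and with the dose table. State whether doses are whole capsules. Correct the 0.7 mg/kg floor statement or withdraw it. Which dose rule to adopt is for the investigators.

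In the report, tabulate achieved mg/kg at months 0, 6 and 12 by entry weight. The visit weights, recorded dose changes and returned-capsule counts needed are already collected. The cost is an amendment to the dosing text and, if needed, the table; no new data are required.
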